## 7 SUBGROUP ANALYSES

TABLE 5 DUMMY TABLE FOR THE SUBGROUP ANALYSIS OF THE PRIMARY OUTCOME

| VARIABLE           | HAZARD RATIO | 95% LOWER C.I. | 95% UPPER C.I. |
|--------------------|--------------|----------------|----------------|
| Treatment          |              |                |                |
| Practice:          |              |                |                |
|                    |              |                |                |
| Subgroup           |              |                |                |
| Subgroup×Treatment |              |                |                |

All subgroup analyses are exploratory and will be conducted on the primary outcome only and on the ITT population.

The efficacy of the intervention by each subgroup will be examined separately. Subgroups to be tested include:

1. Presence/absence of type II diabetes at baseline
2. Presence/absence of coronary artery disease at baseline
3. Diastolic and/or systolic blood pressure above/below the NICE targets at baseline (Defined as- People aged under 80 years: lower than 140/90 mm Hg (systolic/diastolic), People aged over 80 years: lower than 150/90 mm Hg (systolic/diastolic))

We will include appropriate subgroup by treatment interaction terms and add these terms to the Cox regression model used in the primary outcome analysis.

## 8 SAFETY ANALYSIS

TABLE 6 DUMMY TABLE FOR ADVERSE EVENT RECORDING

|                                                                                                                                              | TREATMENT
(N=) | CONTROL
(N=) | OVERALL |
|----------------------------------------------------------------------------------------------------------------------------------------------|-------------------|-----------------|---------|
|                                                                                                                                              | SUMMARY           | SUMMARY         | SUMMARY |
| Number of adverse events                                                                                                                     |                   |                 |         |
| Number of participants experiencing an adverse event                                                                                         | N(%)              | N(%)            | N(%)    |
| Fisher's exact test (P-value)                                                                                                                |                   |                 |         |
| Number of serious adverse events                                                                                                             |                   |                 |         |
| Number of participants experiencing a serious adverse event                                                                                  | N(%)              | N(%)            | N(%)    |
| Fisher's exact test (P-value)                                                                                                                |                   |                 |         |
| Number experiencing Hyperkalaemia                                                                                                            | N(%)              | N(%)            | N(%)    |
| Fisher's exact test (P-value)                                                                                                                |                   |                 |         |
| Maximum potassium level:                                                                                                                     | N(%)              | N(%)            | N(%)    |
| 
 
• <5.5mmol/l
 
• 5.5-5.9mmol/l
 
• 6.0-6.4mmol/l
 
• >6.5mmol/l
 
 |                   |                 |         |
| Fisher's exact test (P-value)                                                                                                                |                   |                 |         |

Occurrence of adverse events and type of adverse events will be recorded in the variable AETERM. Number of adverse effects will be tabulated according to randomised group assignments and the proportions will be compared using Fisher's exact test. Instances of hyperkalaemia will be tabulated by treatment arm and proportions experiencing hyperkalaemia will be compared using Fisher's exact test.

TABLE 7 TYPE OF ADVERSE EVENTS BY GROUP

|                                | TREATMENT
(N=) | CONTROL
(N=) | OVERALL
(N=) |
|--------------------------------|-------------------|-----------------|-----------------|
| Number of events               |                   |                 |                 |
| Hyperkalaemia                  | N                 | N               | N               |
| Deterioration of renal disease | N                 | N               | N               |
| Hypotension        | N                 | N               | N               |
| Other adverse event:           | N                 | N               | N               |
| - Details                      |                   |                 |                 |
| Number of participants         |                   |                 |                 |
| Hyperkalaemia                  | N(%)              | N(%)            | N(%)            |

|                                   | TREATMENT
(N=) | CONTROL
(N=) | OVERALL
(N=) |
|-----------------------------------|-------------------|-----------------|-----------------|
| Deterioration of renal disease    | N(%)              | N(%)            | N(%)            |
| Hypotension                       | N(%)              | N(%)            | N(%)            |
| Other adverse event:
- Details | N(%)              | N(%)            | N(%)            |

Defined as <100mmHg systolic or >20 mmHg systolic drop on standing

The safety analysis will focus on the adverse events. The safety population will include all participants who took at least one tablet of the study medication. Safety monitoring will invoke discontinuation rules for hyperkalaemia, deterioration of renal disease and hypotension. These will be recorded in the adverse event report form in the variable AETERM. These will be summarised by treatment arm as shown in table 11.

All adverse events (AEs) will be recorded at trial visits on the adverse event report form for the initial 6 months of follow-up by the member of the Research Team conducting that visit for the previous inter-visit period. Following this initial 6 month period, only the following AEs will be monitored by the member of the Research Team performing that visit in accordance with PC-CTU SOP TM19 "Pharmacovigilance": enlargement of breasts in men and women; erectile dysfunction; irregular periods; vaginal bleeding after the menopause; deepening of the voice in women, change in the tone of voice in men; excessive hair growth; tiredness; palpitations; and numbness and tingling.

All serious adverse events (SAEs) occurring during the study, either observed by the recruiting GP or reported by the participant, whether or not attributed to study medication, will be recorded on the CRF. The severity of adverse events will be assessed on the following scale: 1=mild; 2=moderate; 3=severe.

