| Serious Adverse Event (SAE)    | 
A serious adverse event is any untoward medical occurrence that:
 
 
• results in death
 
• is life-threatening
 
• requires inpatient hospitalisation or prolongation of existing hospitalisation
 
• results in persistent or significant disability/incapacity
 
• consists of a congenital anomaly or birth defect*.
 
 
Other 'important medical events' may also be considered a serious adverse event when, based upon appropriate medical judgement, the event may jeopardise the participant and may require medical or surgical intervention to prevent one of the outcomes listed above.
 
NOTE: The term "life-threatening" in the definition of "serious" refers to an event in which the participant was at risk of death at the time of the event; it does not refer to an event which hypothetically might have caused death if it were more severe.
 
*NOTE: Pregnancy is not, in itself an SAE. In the event that a participant or his/her partner becomes pregnant whilst taking part in a clinical trial or during a stage where the fetus could have been exposed to the medicinal product (in the case of the active substance or one of its metabolites having a long half-life) the pregnancy should be followed up by the investigator until delivery for congenital abnormality or birth defect, at which point it would fall within the definition of "serious".
 |

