#### **11.5.1. Events exempt from immediate reporting as SAEs**

All SAEs will be reported to the PC-CTU from randomisation until 30-days after the participants' last dose/ last visit (as above)

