### 2.2.1 PRIMARY OUTCOME

Time from randomisation until the first occurring of death or hospitalisation for heart disease (coronary heart disease, arrhythmia, atrial fibrillation, sudden death, resuscitated sudden death), stroke, transient ischaemic attack, peripheral arterial disease or heart failure or first onset of any condition listed above not present at baseline. Primary endpoints will be adjudicated by an independent endpoints committee blinded to treatment arm.

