## 8.3 SERIOUS ADVERSE EVENTS

TABLE 11 TABLE OF SERIOUS ADVERSE EVENTS BY TREATMENT GROUP AND SYSTEM ORGAN CLASS

|                     | TREATMENT
(N%) | CONTROL
(N%) | OVERALL |
|---------------------|-------------------|-----------------|---------|
| SYSTEM ORGAN CLASS: |                   |                 |         |
|                     |                   |                 |         |

A summary of percentages of SAEs by treatment group, system organ class will be prepared for the safety population. No statistical tests will be conducted. A data listing of SAEs will also be prepared, displaying details of patient baseline characteristics and details of the event(s) captured on the CRF.

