#### 8.4.3 SERIOUS ADVERSE EVENT (SAE)

A serious adverse event is any untoward medical occurrence that at any dose:

- Results in death,
- Is life-threatening, NOTE: The term "life-threatening" in the definition of "serious" refers to an event in which the participant was at risk of death at the time of the event; it does not refer to an event which hypothetically might have caused death if it were more severe.
- Requires inpatient hospitalisation or prolongation of existing hospitalisation,
- Results in persistent or significant disability/incapacity, or
- Is a congenital anomaly/birth defect.
- Other important medical events. NOTE: Other events that may not result in death, are not life threatening, or do not require hospitalisation, may be considered a serious adverse event when, based upon appropriate medical judgement, the event may jeopardise the patient and may require medical or surgical intervention to prevent one of the outcomes listed above.

To ensure no confusion or misunderstanding of the difference between the terms "serious" and "severe", which are not synonymous, the following note of clarification is provided:

“The term "severe" is often used to describe the intensity (severity) of a specific event (as in mild, moderate, or severe myocardial infarction); the event itself, however, may be of relatively minor medical significance (such as severe headache). This is not the same as "serious," which is based on patient/event outcome or action criteria usually associated with events that pose a threat to a participant's life or functioning as defined in the bullet points above. Seriousness (not severity) serves as a guide for defining regulatory reporting obligations.”

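### The only between-arm test restricted to SAEs pools primary-endpoint deaths and cardiovascular admissions with all other serious events, so a real benefit could offset serious harm outside the separately analysed effects

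*Combined protocol and SAP*

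**What the plan says.** **Endpoint.** SAP 2.2.1 defines the primary outcome as "Time from randomisation until the first occurring of death or hospitalisation for heart disease" and the other listed cardiovascular conditions, or first onset of any of them. Death counts whatever its cause (Protocol 7.1).

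**SAE definition.** Protocol 11.1 and SAP 8.4.3 both list death and any event that "requires inpatient hospitalisation or prolongation of existing hospitalisation".

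**Recording.** SAP section 8 says SAEs, "whether or not attributed to study medication, will be recorded on the CRF". Protocol 11.5.1, the section set aside for exempt events, exempts none: "All SAEs will be reported to the PC-CTU from randomisation until 30-days after" the last dose or visit.

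**Analysis.** SAP Table 6 has a row for "Number of participants experiencing a serious adverse event", followed by a Fisher's exact test row. SAP 8.3 adds a breakdown: "A summary of percentages of SAEs by treatment group, system organ class will be prepared for the safety population". That table carries no tests, and endpoint events stay in it.

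**Other safety analyses.** Hyperkalaemia and maximum potassium band each have a Fisher test (Table 6). Hypotension has a log-binomial model (SAP 4.2.2) and eGFR a linear mixed model (SAP 4.2.3). Table 7 counts hyperkalaemia, renal deterioration and hypotension by arm. AE severity is compared and relatedness tabulated (SAP 8.1).

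**The concern.** A comparison of participants with any SAE is normally read as a check on serious harm. Here, much of what it counts is the efficacy outcome. If spironolactone prevents deaths and cardiovascular admissions, the treated arm's SAE proportion falls for that reason alone, and a rise in other serious events can be cancelled within the same row. If it prevents nothing, the endpoint events still add a large common background that weakens the contrast.

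The SAE row carries particular weight in this trial. After the first 6 months, non-serious adverse events are recorded only from a short list of symptoms and laboratory or blood-pressure thresholds (Protocol 11.4). For the remaining 30 of 36 months, SAE reporting is the only broad capture of harm. Serious toxicity not on that list, and not among the separately analysed effects, reaches a between-arm SAE test only through the row that also carries efficacy.

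**Working it through.** **Inputs from the documents.** Control rate 13.4 per 100 person-years, 3 years, hazard ratio (HR) 0.80, 13% treatment withdrawal, printed diluted effect 0.84, two-sided 5%, 80% power, 10% attrition, 1511 per arm (Protocol 12.3). The planning rate counts cardiovascular hospitalisations and deaths only, so all of it is SAE-type.

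**Assumed, not in the documents.** Control risk *q* of other SAEs, 5 to 30%, independent of endpoint events.

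**1. Reproduce the plan's figure.** Events = 4(1.960 + 0.842)² / (ln HR)². Diluting the log hazard ratio by 13% gives 0.8^0.87 = 0.8235 and 833 events. Three-year risks are 1 − exp(−0.402) = 0.331 and 1 − exp(−0.402 × 0.8235) = 0.282. Then 833 / (0.331 + 0.282) = 1359, and 1359 / 0.9 rounds up to 1511 per arm, an exact match. The printed 0.84 gives about 1859 by the same route, so HR 0.80 and 0.84 are both carried forward as a bracket.

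**2. Endpoint risk at 3 years.**
- Control: 33.1%, about 500 of 1511.
- HR 0.80: 1 − exp(−0.402 × 0.80) = 27.5%, about 416.
- HR 0.84: 1 − exp(−0.402 × 0.84) = 28.7%, about 433.

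**3. Break-even excess.** P(any SAE) = 1 − (1 − endpoint risk)(1 − other-SAE risk). Setting the arms equal, the excess of other SAEs that is fully offset is (1 − q) × [1 − (1 − p_control)/(1 − p_treated)]. The bracket is 0.0773 at HR 0.80 and 0.0623 at HR 0.84 (from unrounded risks).
- HR 0.80: 0.95 × 0.0773 = 7.3 points at q = 5%; 0.70 × 0.0773 = 5.4 points at q = 30%.
- HR 0.84: 0.95 × 0.0623 = 5.9 points at q = 5%; 0.70 × 0.0623 = 4.4 points at q = 30%.
- If the two kinds of event never occur in the same person, the offset is the difference in endpoint risk: 5.6 points (HR 0.80) or 4.4 points (HR 0.84).

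**4. A true 5-point excess of other SAEs, 1511 per arm, Fisher's test on expected counts (spironolactone v control).**

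| q | Any SAE, HR 0.80 | Any SAE, HR 0.84 | Other SAEs only |
|---|---|---|---|
| 10% | 580 v 601, P = 0.46 | 595 v 601, P = 0.85 | 227 v 151, P = 0.00004 |
| 20% | 689 v 702, P = 0.66 | 703 v 702, P = 1.00 | 378 v 302, P = 0.001 |
| 30% | 799 v 803, P = 0.91 | 810 v 803, P = 0.83 | 529 v 453, P = 0.004 |

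Power for the endpoint-excluded comparison is about 99%, 91% and 83%.

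**5. No benefit (HR 1.0), same 5-point excess.** Any SAE: 652 v 601, 753 v 702 and 854 v 803, with P = 0.065, 0.069 and 0.068. Power is only 45 to 46%, because of dilution rather than masking.

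**6. Lower event rate.** The supplement's post hoc analysis excluding PAD has a control rate of 5.37 per 100 years. Endpoint risk would then be 14.9% v 12.1% at HR 0.80, and the break-even excess falls to 2.2 to 3.0 points for q = 30% to 5%.

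**The case against.** **The expected toxicities are analysed elsewhere.** A reader might infer that serious hyperkalaemia, renal or hypotensive harm would be hidden. The documents do not support that: each has its own analysis, and cardiovascular benefit does not offset those comparisons. They use thresholds or mean change rather than seriousness, but they would show the signal. This stands and narrows the gap to other serious harm.

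**The any-SAE P-value is not decisive.** A reader might also infer that the safety objective would be answered by this row. The stated safety outcomes are hypotension, adverse events and hyperkalaemia (SAP 1.4), and nothing makes the SAE test the verdict on safety. This also stands.

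**The all-SAE row is legitimate.** It summarises total serious burden, and mortality belongs in safety reporting. That is why it should stay.

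**Removing endpoint events can remove harm.** Any death is an endpoint, so fatal toxicity would leave the new row, as would an arrhythmia admission caused by the drug. The adjudication variable DECISION is also unsuitable as the sole flag: it is No for events that are not the first, and for insufficient information (SAP 2.2.2), so repeat cardiovascular admissions would remain. These points are right and shape the fix.

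**The size is assumed.** Other-SAE risks and independence are not in the documents. The 1511 per arm is the planned randomised number, whereas the SAP's safety population is those who took at least one tablet and the supplement's adverse-event table has 388 v 984. The P-values are therefore illustrative; the break-even excess does not depend on sample size.

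**Conclusion.** The point holds as a gap in the plan. Table 6's any-SAE row is the only SAE-restricted between-arm test, and it mixes efficacy events with other serious harm. At the planned rate and HR 0.80 to 0.84, it could conceal a rise of about 4 to 7 points in other SAEs, given a control risk of 5 to 30% and independence. Under no benefit it has a little under half the power to detect a 5-point rise at 1511 per arm.

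Three stronger readings are not supported:
- That all serious toxicity could be hidden. The named effects have unaffected analyses, so what is exposed is serious harm outside them, which is separated only in the untested organ-class table.
- That every endpoint event is an SAE. First onset without admission need not be, and endpoint events found outside the 30-day reporting window or outside the safety population are narrow exceptions.
- That masking occurred in this trial. Masking needs benefit, and the supplement's post hoc hazard ratios are 1.01 and 0.99 (the latter from 94/677 v 96/695, excluding PAD). They suggest little masking in the data; the weakness is in the plan.

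**What to change.** In SAP Table 6 and section 8.3:
- Keep the all-SAE row.
- Add a row for participants with at least one SAE that is neither a death nor an admission for a listed endpoint condition, by arm, with risk difference and 95% CI.
- Define the flag by event type, treating first and repeat cardiovascular admissions alike, and not by DECISION alone.
- Show all-cause deaths, and SAEs judged related to treatment, in separate rows so that fatal or arrhythmic toxicity is not lost. Relatedness is judged open-label, so that row supports the others and does not replace them.
- State that the new row is read beside the all-SAE row, not in place of it.

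The cost is one derived flag and a few table rows. SAEs are already recorded on the CRF with a description and relatedness, so no new data collection is needed.

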## 12.2. Description of Statistical Methods

In accordance with CONSORT guidelines, we will record and report participant flow. Descriptive statistics of recruitment, drop-out, and completeness of interventions will be provided. Baseline variables will be presented by randomised group using frequencies (with percentages) for binary and categorical variables and means (and standard deviations) or medians (with lower and upper quartiles) for continuous variables. There will be no tests of statistical significance nor confidence intervals for differences between groups on any baseline variables.

The primary analysis will be on an intention-to-treat basis. That is, after randomisation, participants will be analysed according to their allocated treatment group irrespective of what treatment they actually receive. The primary outcome will be analysed using a survival analysis method, such as Cox proportional-hazards model, adjusting for practices. Results will be presented as hazard ratios with 95% confidence intervals and associated two-sided P-values. To test the robustness of the result, a sensitivity analysis will be carried out, using the same method, adjusting the following pre-specified baseline prognostic factors: diastolic and/or systolic blood pressure above or below NICE target, type II diabetes and coronary artery disease.

Same approach will be repeated for individual components of the primary composite endpoint and all-cause mortality as secondary analyses. Analyses for other outcomes will be carried out using multiple log-binomial regression models for binary data and linear mixed effect model for continuous data collected over time.

Assumption of proportional hazards will be examined and if any of the assumptions were violated, a suitable alternative survival method will be considered. Similarly, alternative methods will be considered if any violation of assumptions is detected in any of the aforementioned methods for other outcomes.

Adverse effects will be tabulated according to randomised group assignments and the proportions will be compared using Fisher's exact test.

A full detailed analysis plan, including approach of handling missing data, subgroup analyses, and sensitivity analyses, and a plan for interim analysis will be prepared before the final datalock and analysis by a statistician who is independent from the study. All analyses will be performed by the trial statistician and validated by a separate statistician.

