#### 2.2.3.4 TO DETERMINE THE SAFETY OF ARA IN PATIENTS WITH STAGE 3b CKD

##### Endpoints:

- (a) Rates of adverse events. All adverse events are recorded in the AE report CRF. The number of participants experiencing at least one AE and the number of AEs per participant will be reported. Number of SAEs will also be reported. Rates of hyperkalaemia:
- (b) Hyperkalaemia is defined as a potassium level  $\geq 5.5\text{mmol/l}$ . Potassium [K] is recorded at each visit. A binary variable will be derived as experiencing hyperkalaemia at any time point. Hyperkalaemia will be recorded as “yes” if the participant has potassium levels  $\geq 5.5\text{mmol/l}$  at any point during the study and “no” if at least one potassium measure is recorded and it does not meet the definition of hyperkalaemia. If a participant has hyperkalaemia at any point during the study, the maximum value of Hyperkalaemia for that patients will be used to derive a second variable to indicate whether the maximum hyperkalaemia was mild ( $5.5\text{-}5.9\text{mmol/l}$ ), moderate ( $6.0\text{-}6.4\text{mmol/l}$ ) or severe ( $>6.5\text{mmol/l}$ ).

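### For any AE, any SAE and hyperkalaemia the plan gives only N(%) per arm and a Fisher P-value, with no effect estimate or confidence interval

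*Combined protocol and SAP*

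**What the plan says.** SAP 2.2.3.4 sets the objective: "TO DETERMINE THE SAFETY OF ARA IN PATIENTS WITH STAGE 3b CKD". Hyperkalaemia is a potassium of 5.5 mmol/L or more, reduced to one yes/no per participant: "A binary variable will be derived as experiencing hyperkalaemia at any time point".

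The comparison is set in SAP section 8: "Instances of hyperkalaemia will be tabulated by treatment arm and proportions experiencing hyperkalaemia will be compared using" Fisher's exact test. Table 6 has rows for any AE, any SAE ("Number of participants experiencing a serious adverse event"), hyperkalaemia and maximum potassium in four classes. Each gets N(%) per arm and a Fisher P-value; there is no column for an effect estimate or interval. Protocol 12.2 agrees: "Adverse effects will be tabulated according to randomised group assignments and the proportions will be compared using Fisher's exact test". SAP 8.1 adds a chi-squared or Fisher test on severity, and SAP 8.2 and 8.3 are descriptive without tests.

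Other binary outcomes are handled differently. SAP 4.2.2 analyses hypotension, which the objectives table also lists under safety, by log-binomial regression with a relative risk, 95% CI and P-value. The footnote to SAP Table 2 says that binary outcomes are reported as relative risks. Protocol 12.2 assigns log-binomial models to other binary outcomes in general.

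**The concern.** A Fisher P-value tests whether the two proportions are equal. It does not say how large an excess is, or how large an excess the data still allow. For harms the second quantity is usually the one wanted, because a non-significant result can come from no excess or from an excess estimated too imprecisely to detect.

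Neither document states a power or precision for any safety comparison; the sample size was set on the primary efficacy endpoint. Leaving the effect measure and interval unspecified also means that both would be chosen after the counts are known. The plan already does better for hypotension under the same objective, so the gap is one of internal consistency as well as method.

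**Working it through.** **Inputs from the documents.** 1:1 allocation and 1511 per arm with 10% attrition (protocol synopsis and 12.3), so 1511 × 0.9 ≈ 1360 per arm after attrition; two-sided 5% (protocol 12.7).

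**Inputs that are assumptions.** All event rates by arm. Protocol 9.8 cites 2% serious hyperkalaemia in a severe heart failure trial of spironolactone, and potassium above 5.5 mmol/L in 10% of eplerenone patients with reduced GFR in a post-infarction trial. Neither is a rate for this population, so a range is shown. The calculations ignore clustering by practice.

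**The plan's own figure.** There is no safety figure to reproduce. The 1511 is an efficacy size. Diluting HR 0.80 by 13% withdrawal gives 1 − 0.20 × 0.87 = 0.826, and events = 4(1.96 + 0.84)²/(ln 0.826)² ≈ 860. The 3-year event probabilities at 0.134 per year are 0.331 and 0.282, so 860/0.613 ≈ 1402 per arm. Allowing for 10% loss gives 1472 to 1557 depending on the method, which brackets 1511. (The diluted effect printed in protocol 12.3, 0.84, would need 1757 to 1858.) I take 1511 as given.

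**Step 1: what a non-significant Fisher result leaves open.** For c control and t treated cases with n = 1511 per arm:

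- RR = t/c, with SE(ln RR) = √(1/t − 1/n + 1/c − 1/n) and upper limit RR × exp(1.96 × SE).
- RD = (t − c)/n, with the Newcombe interval.

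For 30 v 48: RR = 1.60; SE = √(1/48 + 1/30 − 2/1511) = 0.230; upper limit 1.60 × exp(0.451) = 2.51. RD = 18/1511 = 1.19 points, upper limit 2.36.

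For 15 v 28: RR = 1.87; SE = √(1/28 + 1/15 − 2/1511) = 0.318; upper limit 1.87 × exp(0.623) = 3.48. RD = 13/1511 = 0.86 points, upper limit 1.76.

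The table takes the largest treated count that still gives Fisher P>0.05 at each assumed control rate.

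| Control v treated cases | Rates | Fisher P | RR upper limit | RD upper limit (points) |
|---|---|---|---|---|
| 15 v 28 | 1.0% v 1.9% | 0.064 | 3.5 | 1.8 |
| 30 v 48 | 2.0% v 3.2% | 0.0505 | 2.5 | 2.4 |
| 151 v 185 | 10.0% v 12.2% | 0.056 | 1.50 | 4.5 |
| 302 v 347 | 20.0% v 23.0% | 0.051 | 1.32 | 5.9 |

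Even with equal counts of 15 v 15 (P=1), the RR upper limit is 2.0. Table 6 as planned would show none of these limits.

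**Step 2: how far power varies.** Exact two-sided Fisher power at 1511 per arm (1360 in brackets):

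| Assumed control v treated | Power |
|---|---|
| 2% v 3% | 38% (34%) |
| 20% v 23% | 50% (46%) |
| 1% v 2% | 57% (52%) |
| 7% v 10% | 83% (78%) |
| 2% v 4% | 88% (85%) |
| 20% v 25% | 90% (87%) |
| 5% v 10% | 99.9% (99.9%) |

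Power depends almost wholly on the assumed rates, so it does not measure the defect. Interval width (step 1) does, because that is what the plan leaves out.

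**The case against.** The strongest reply is that hyperkalaemia may already be covered. It is a listed secondary outcome, protocol 12.2 assigns log-binomial models to other binary data, and the SAP Table 2 footnote specifies relative risks. This has some force: for hyperkalaemia the documents can be read as inconsistent rather than silent. But no subsection of SAP 4.2 applies that model to hyperkalaemia, and section 8 expressly assigns Fisher's test. For any AE and any SAE, the specific text names only Fisher's test.

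A second reply is that N(%) per arm is tabulated, so anyone could derive an interval. That is true, but measure, method and emphasis would then not be pre-specified.

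Three stronger readings are tempting, and the documents do not support them.

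- A reader might infer that the whole safety objective rests on Fisher P-values. It does not: hypotension has a relative risk with CI, eGFR has a mean difference with CI, and severity, relatedness, withdrawals and SAEs by organ class are all tabulated.
- A reader might infer that the test misses relevant harms about half the time. That fits 1% v 2% or 20% v 23% but not 2% v 4% or 5% v 10%, and no smallest relevant harm is stated. Low rates taken from the cited serious-hyperkalaemia figure also do not match the SAP's two-group endpoint, which is potassium of 5.5 mmol/L or more.
- A reader might infer that P>0.05 will be taken to mean safe. No passage sets that rule, and SAP 4.7 calls the secondary outcomes exploratory.

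It is also fair to say that an interval adds no power. It shows the uncertainty and does not reduce it.

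**Conclusion.** The point holds for any AE, any SAE and hyperkalaemia. The specific safety text plans percentages and a Fisher P-value, and pre-specifies no effect estimate or interval, while hypotension under the same objective has both. The consequence is that Table 6 would not show how much excess harm remains compatible with the data: at 1511 per arm, a non-significant result can coexist with a risk ratio upper limit of 2.5 at an assumed 2% control rate, or 3.5 at 1%. At higher control rates the relative limit tightens (1.32 at 20%) but the absolute limit widens (5.9 points).

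These figures rest on assumed control rates, the planned size and equal denominators. The last is not settled. The SAP defines the safety population as participants who took at least one tablet, which leaves membership of the control column unclear, while section 8 also tabulates by randomised group. This is an improvement worth making to reporting and interpretation. It does not show that the safety assessment would fail.

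**What to change.** In SAP section 8 and Table 6, and in protocol 12.2:

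- Report the risk difference and risk ratio, each with 95% CI, by randomised group, for any AE, any SAE, hyperkalaemia (potassium 5.5 mmol/L or more) and potassium of 6.0 mmol/L or more.
- Keep Fisher's P as a supplementary column.
- State that these harms will be interpreted from the interval and not from non-significance.
- Name the interval methods and the denominators. Naming the method matters because Fisher's test is conservative: for 30 v 48 cases the log-method RR interval is 1.02 to 2.51, which excludes 1 although P=0.0505. The SAP should say in advance that the interval governs.
- Reconcile section 8 with the general log-binomial rule and the Table 2 footnote, so that hyperkalaemia has one stated analysis.

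The cost is a few sentences and extra columns in Table 6. No new data are needed, but the control-arm denominator must be defined first.
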